### Measurements - outcomes

Questionnaires for each patient will be filled in and data will be collected at the baseline and 2, 5.5, 9, and 12 months later to assess the outcomes of the intervention. The primary outcome measurement is the number of ED visits. Secondary outcome measurements are the standardized measurements of health status via EuroQol (EQ-5D) [51,52] and WHOQOL-BREF, cost analysis based on the use of health services, and an instrument on feelings of discrimination. (Figure 4).

**Figure 4 F4:**
[figure not shown]
Timetable of the assessments: timetable for every ED-FU included in the study with outcome assessment (2, 5.5, 9, and 12 months for the intervention and the control group).

#### Primary outcome: number of ED visits

The primary outcome will be the number of ED visits made by FUs. This information will mainly be available via the Lausanne hospital/ambulatory electronic records system and hospital/ambulatory administrative databases covering a period of 12 months after the initial emergency department visit.

“Care Notebooks” in hands of case and control participants will also be generated from the beginning of the study. Patients will be asked to report all visits (ED visits to any hospital and all outpatient visits) in their Care Notebook during the 12 months following their first visit (Figure 3). Patients will be contacted by telephone by the nurse researcher to answer questions about their use of the health-care system and to verify that they have completed their Care Notebooks appropriately. If this is not the case, the nurse researcher will help the patient find methods and strategies for improving their reporting. If necessary, incentives would be used to help FU patients complete Care Notebooks appropriately. The quality control will be repeated at 2-, 5.5-, 9-, and (finaly) 12-month follow-ups. Confirmatory telephone calls to other hospitals, medical institutions, or private practices that the patient claims to have visited will be made by the nurse researcher, after obtaining the patient’s written permission to do so.

Moreover, the validity of FU patients’ answers could be assessed by matching their answers to our gold standard electronic records system of visits within our hospital and to the records of the participant’s health insurance provider, after having obtained relevant informed consent.

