#### Secondary outcome: cost analysis

The second outcome measurement focuses on the costs induced due to the health-care resources used by the FU patients. Their health-care consumption is related to services provided by our hospital but we cannot exclude that a FU also uses services provided by other hospitals/institutions in the community (services provided outside our hospital).

1) *Concerning services provided by our hospital*, different hospital administrative databases which record all inpatient and outpatient admissions will allow us to have access to details of all healthcare used by the FU and consequently the related costs. The latter will be composed of costs related to:

a. outpatient resources induced by ED attendances,

b. inpatient resources induced by ED attendances,

c. non-ED related outpatient resources used within the hospital,

d. the ED CM multidisciplinary team intervention.

Access to the accounting analytical systems of our hospital, as well as to the outpatient invoicing department, will allow the necessary information to be collected in order to calculate costs.

2) *Concerning services used outside our hospital*, information recorded in Care Notebooks will help to identify to what extent FUs seek and use services outside our hospital’s boundaries, including whether patients use EDs of other hospitals, etc. The Care Notebook, by recording the date and the location of all visits the FU makes, will also help identify the types of services (health and/or social services) used by FUs.

The CM intervention may affect how the FUs use the health care system in general. The primary outcome of the project will allow us to identify whether the CM intervention is associated with a decrease in the number of visits to the ED of our hospital. However, it is also important to investigate to what extent the potential decrease in health-care resources used at the ED of our hospital is (or is not) associated with an increase in health-care resources used outside this specific ED. Consequently, information from the Care Notebook will help capture a substitution effect between health-care utilization at our hospital’s ED and health-care utilization external to this specific ED. Based on average unit costs, costs associated with the health care consumption outlined in the Care Notebook will be simulated.

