Additionally, having obtained the patient’s informed consent we will contact their health insurer or the relevant health services provider in order to collect information on the frequency, type, and cost of health services that the participant has used during the study.

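### The Care Notebook's stated scope does not name inpatient stays at other hospitals, although it is the named source for substitution and for simulated outside-hospital costs

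*Protocol article*

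**What the plan says.** All references are to the protocol article.

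- *Primary outcome: number of ED visits* sets the content of the notebook: "Patients will be asked to report all visits (ED visits to any hospital and all outpatient visits) in their Care Notebook". It adds telephone contact: "Patients will be contacted by telephone by the nurse researcher to answer questions about their use of the health-care system". Checks are made at 2, 5.5, 9 and 12 months, and the nurse researcher, with written permission, rings other institutions that a patient reports having attended.
- *Secondary outcome: cost analysis* gives the notebook three tasks. The first is outside use: "information recorded in Care Notebooks will help to identify to what extent FUs seek and use services outside our hospital’s boundaries". The second is substitution: "information from the Care Notebook will help capture a substitution effect". The third is cost: "Based on average unit costs, costs associated with the health care consumption outlined in the Care Notebook will be simulated".
- The same section lists the study hospital's own cost items, taken from its databases. Inpatient resources that follow from ED attendance are among them.
- It then adds a further source that depends on the patient's agreement: "informed consent we will contact their health insurer or the relevant health services provider". The request covers how often services were used, of what kind and at what cost, with no limit by type of care.
- *The multidisciplinary mobile team CM pattern intervention* includes helping eligible patients obtain health insurance. *Background* describes frequent users as often uninsured.

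**The concern.** The substitution question is whether less use of this ED is matched by more use elsewhere. Admissions are part of that, and the plan treats them as a cost when they occur in-house. *Setting* says that other, non-university hospitals serve the same population, and the cost section accepts that patients may use them. Yet the instrument named for measuring outside use lists ED and outpatient visits only.

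An admission elsewhere then has no stated entry in the notebook-based simulation. Whether it is counted depends mainly on insurer or provider records. Those records will not exist for every patient, and the intervention may itself change who has them. At stake are the substitution conclusion and the cost comparison, and through the latter the cost-utility ratio. The count of ED visits is not affected.

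**Working it through.** **1. Side by side.**

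| Type of use | Study hospital | Elsewhere, notebook | Elsewhere, insurer or provider records |
|---|---|---|---|
| ED visit | hospital databases | named | yes, with consent |
| Outpatient visit | hospital databases | named | yes, with consent |
| Inpatient stay | hospital databases (stays arising from ED attendance) | not named | yes, with consent |

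The inpatient row is the only one in which the notebook has no stated entry.

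**2. What partial capture does to the arm comparison.** Let r be the true rate of outside stays per patient-year, c the proportion captured and u the unit cost, with I for intervention and C for control.

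- True cost difference: u(r_I − r_C)
- Recorded cost difference: u(c_I·r_I − c_C·r_C)
- Recorded minus true: −u[(1 − c_I)·r_I − (1 − c_C)·r_C]

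Three cases follow.

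- Equal rates and equal capture: the error is 0. Both arms' totals are too low, but the difference is right.
- Equal capture c, more outside stays under intervention: the error is −u(1 − c)(r_I − r_C), which is negative. The intervention looks too cheap.
- Equal rates r, better capture under intervention because more patients gain insurance: the error is +u·r·(c_I − c_C), which is positive. The intervention looks too expensive.

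The direction is therefore open. The documents give none of r, c or u.

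**3. Illustration under assumptions only.** The target effect in *Sample size* is 2 ED visits per patient-year, with 125 patients per arm. Assume that one stay costs 10 to 30 times one ED visit.

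- Net excess of stays that equals the target effect in cost: 2/10 = 0.20 to 2/30 = 0.067 per patient-year, or 125 × 0.20 = 25 down to 125 × 0.067 ≈ 8.3 stays per arm.

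Assume also that 10% to 50% of patients have no usable record and that outside stays run at 0.2 to 0.5 per patient-year.

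- Unrecorded stays per arm: 125 × 0.1 × 0.2 = 2.5 to 125 × 0.5 × 0.5 = 31.25.
- Mid-range: 125 × 0.30 × 0.35 ≈ 13.1 unrecorded, against a break-even of 125 × 2/20 = 12.5.

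The second quantity is a whole pool in one arm; the first is a net difference between arms. At the low end the pool is smaller than any break-even value. At mid-range nearly every unrecorded intervention-arm stay would have to be excess over control. The sums also ignore the planned 30% drop-out and any in-house inpatient savings. They show that the gap could matter, not that it does.

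**The case against.** A reader might infer that outside admissions are costed at zero, or that data on them would never be collected. The documents do not support either reading. No section excludes such stays or values them at nil. The insurer or provider request is not restricted by type of care, so it reaches inpatient use and its cost wherever it succeeds, and the insurer route does not require the hospital to be known in advance. An admission that begins in another ED falls within the notebook's scope as an ED visit, with its date and place, and can be followed up by telephone. The nurse's questions about service use are not confined to outpatient care. The cost section also describes the notebook in broader terms, covering types of health and social service.

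A reader might also infer that case management moves admissions to other hospitals. The referrals listed are to in-house mental health departments, community clinicians, substance-abuse services and social help. None is an inpatient admission elsewhere. The provider perspective named in *Statistical methods* also leaves unclear how far stays at other hospitals belong in the cost-utility ratio.

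Much of this stands, and it narrows the point. What remains is the following.

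- An ED entry with a date and place carries no stated length of stay, so an average unit cost applied to it would price a visit rather than an admission. A direct admission has no stated entry.
- The inpatient content of the telephone questions is not stated.
- The insurer or provider route needs consent, and the insurer part needs an insurer. The 30% refugees or undocumented migrants expected in *Sample size* may include uninsured patients, but the article does not give their insurance status.
- Whatever the perspective, the cost section itself plans to examine outside use and substitution.

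**Conclusion.** The point holds as a limited one. The notebook's listed content is narrower than the use the article makes of it, and the missing category is one that the article costs in-house. This is a stated scope, not a detail left to a fuller document. Outside inpatient stays would be captured mainly through consent-dependent records, so they may be missed for some patients. Capture could differ by arm because the intervention helps patients gain insurance; that is a plausible mechanism, not one the article reports.

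Neither the size nor the sign of any bias can be derived, and the illustrative ranges rest wholly on assumed cost ratios, record coverage and stay rates. The substitution comparison and the cost results are exposed; the primary outcome is not. This is a worthwhile, inexpensive improvement to a secondary analysis and does not threaten the trial's main conclusion.

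**What to change.** In *Primary outcome: number of ED visits*, add inpatient stays at any hospital or institution to the notebook (dates or nights, place, type of stay). Put the same item in the nurse researcher's questions at 2, 5.5, 9 and 12 months. Use identical wording and effort in both arms, so that capture does not depend on insurance status or allocation.

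In *Secondary outcome: cost analysis*, cost these stays at average unit costs within the outside-hospital simulation and count them in the substitution comparison. Use insurer or provider records to confirm them where available.

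The cost is one more notebook section, one more question in four contacts already planned, and one average inpatient unit cost. The downside is slightly more burden for patients and some self-report error. No extra patients, staff or visits are needed.

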#### Secondary outcome: cost analysis

The second outcome measurement focuses on the costs induced due to the health-care resources used by the FU patients. Their health-care consumption is related to services provided by our hospital but we cannot exclude that a FU also uses services provided by other hospitals/institutions in the community (services provided outside our hospital).

1) *Concerning services provided by our hospital*, different hospital administrative databases which record all inpatient and outpatient admissions will allow us to have access to details of all healthcare used by the FU and consequently the related costs. The latter will be composed of costs related to:

a. outpatient resources induced by ED attendances,

b. inpatient resources induced by ED attendances,

c. non-ED related outpatient resources used within the hospital,

d. the ED CM multidisciplinary team intervention.

Access to the accounting analytical systems of our hospital, as well as to the outpatient invoicing department, will allow the necessary information to be collected in order to calculate costs.

2) *Concerning services used outside our hospital*, information recorded in Care Notebooks will help to identify to what extent FUs seek and use services outside our hospital’s boundaries, including whether patients use EDs of other hospitals, etc. The Care Notebook, by recording the date and the location of all visits the FU makes, will also help identify the types of services (health and/or social services) used by FUs.

The CM intervention may affect how the FUs use the health care system in general. The primary outcome of the project will allow us to identify whether the CM intervention is associated with a decrease in the number of visits to the ED of our hospital. However, it is also important to investigate to what extent the potential decrease in health-care resources used at the ED of our hospital is (or is not) associated with an increase in health-care resources used outside this specific ED. Consequently, information from the Care Notebook will help capture a substitution effect between health-care utilization at our hospital’s ED and health-care utilization external to this specific ED. Based on average unit costs, costs associated with the health care consumption outlined in the Care Notebook will be simulated.

Additionally, having obtained the patient’s informed consent we will contact their health insurer or the relevant health services provider in order to collect information on the frequency, type, and cost of health services that the participant has used during the study.

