### Statistical methods

Groups will be compared from their initial allocation independently of eventual crossover (intention-to-treat analyses). The principle measurement of effect is an individual’s average reduction in visits to the ED over 12 months compared to the number of visits observed in the control group. This will be calculated using linear regression with number of visits during 12 months’ follow-up as an independent variable, and group allocation and yearly number of ED visits prior to intervention as dependent variables. Should group imbalance occur, secondary analysis will test the confounding effects by measuring the effect after adjusting for these confounding effects in the linear regression. Known determinants of frequent use are to be considered as potential confounders if, by chance due to the randomisation, we are to observe a relative difference of 20% between groups.

FUs are known to visit EDs on regular bases over a short period of time [55] (regression to the mean), so we also expect to see a decrease in the number of visits in the control group. Our analysis will measure the true effects of the intervention taking this phenomenon into consideration.

In terms of medico-economic analysis, benefits of the care management program will be evaluated by health gains expressed in Quality Adjusted Life Years (QALYs) over the 12-month period. A cost-utility analysis from the health-care provider perspective will be conducted by combining the use of two outcomes (i.e. costs and health status in terms of quality of life). A cost-utility ratio will then be calculated. A sensibility analysis will also be conducted in order to estimate the confidence interval for the cost-utility ratio. Uncertainty will be assessed by univariate and probabilistic sensitivity analysis (Monte Carlo simulation). All statistical analysis will be carried out with STATA 12.0, Statacorp, College Station, Texas, USA.

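### The in-hospital cost list leaves out inpatient stays that do not start in the ED, and the provider perspective is not reconciled with the outside-hospital costs

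*Protocol article*

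**What the plan says.** The section of the protocol article on the cost-analysis outcome describes the in-hospital source broadly: "different hospital administrative databases which record all inpatient and outpatient admissions will allow us to have access to details of all healthcare used by the" frequent users. It then lists what the related costs consist of:

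- (a) outpatient care that follows from an ED visit
- (b) inpatient care, but only in the form of "inpatient resources induced by ED attendances"
- (c) other hospital outpatient care, given as "non-ED related outpatient resources used within the hospital"
- (d) the case management team itself

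For care elsewhere, the same section relies on the Care Notebook, which "will help capture a substitution effect between health-care utilization at our hospital" (its ED) and care outside that ED. The cost of notebook care is to be simulated from average unit costs. With the patient's consent, the team will also approach insurers or providers to "collect information on the frequency, type, and cost of health services that the participant has used during the study".

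The Statistical methods section then fixes a viewpoint: "A cost-utility analysis from the health-care provider perspective will be conducted". It does not list the cost streams that this viewpoint admits. Under Aims and hypotheses there are two economic comparisons: cost against ED attendance, and cost against QALYs.

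**The concern.** The list splits outpatient care into ED and non-ED parts and counts both. It makes the same split for inpatient care and counts only one part. A planned, direct or referred admission to the same hospital has no place in items (a) to (d).

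This matters because the missing category is defined by the route into hospital, and the intervention works on that route. The section on the case management intervention has the team refer patients to mental health departments inside the hospital, to psychiatrists and to general practitioners. If some admissions that would have begun in the ED begin by referral instead, their cost leaves the account in the intervention arm although the care was still given. A cost definition that can depend on the allocated arm can produce a difference where there is none, or distort a real one.

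The second part is a gap between sections. The article plans to measure and cost outside care in order to see whether ED savings reappear elsewhere. It then names a provider perspective for the cost-utility analysis without saying whether those outside costs belong in the ratio. If that is left open, the cost set could be chosen after the results are known.

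**Working it through.** The article states no figure for the cost analysis, so there is nothing to reproduce. The check sets the cost streams side by side and then shows the form of the bias.

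**Coverage of each stream, as written**

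| Stream | Where it is covered |
|---|---|
| Hospital outpatient, ED-induced | Item (a) |
| Hospital outpatient, not ED-related | Item (c) |
| Hospital inpatient, ED-induced | Item (b) |
| Hospital inpatient, not ED-induced | In no item, though the databases record it |
| Case management team | Item (d) |
| Outside ED and outpatient visits | Care Notebook, simulated from unit costs; insurer or provider data with consent |
| Outside inpatient stays | Not named in the notebook's scope (section on the primary outcome); insurer or provider data with consent |

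Could another source fill the fourth row? The notebook is described as covering ED visits to any hospital and all outpatient visits, so it does not clearly do so. Insurer or provider data could, but they depend on consent and, for insurer data, on being insured. The Sample size section expects 30% of patients to be refugees or undocumented migrants, and the intervention includes help in obtaining insurance. Incomplete insurer coverage is therefore plausible, although the article gives no rate.

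**Form of the bias**

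Let M be the mean cost per patient from items (a) to (d), and E the mean cost per patient of hospital stays not induced by an ED attendance. Let I and C mark the intervention and control arms.

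- Measured saving: S = M_C − M_I
- True in-hospital saving: S − (E_I − E_C)
- Overstatement of the saving: E_I − E_C

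Non-ED stays that are equally frequent and costly in both arms cancel. Only the difference between the arms matters.

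For pure re-routing, suppose p stays per intervention patient, each costing k, start by referral instead of in the ED. Then M_I falls by p × k, E_I rises by p × k, and true cost is unchanged. The spurious saving is p × k. The article gives neither p nor k.

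The same result as a share: if a share f of the measured saving reappears as uncosted stays, the true saving is (1 − f) × S. Per 100 units of measured saving, with f assumed across its possible range:

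- f = 0: 100 × (1 − 0) = 100
- f = 0.25: 100 × (1 − 0.25) = 75
- f = 0.5: 100 × (1 − 0.5) = 50
- f = 1: 100 × (1 − 1) = 0

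If case management instead lowered planned admissions, E_I − E_C would be negative and the omission would understate the saving.

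**Perspective**

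The provider perspective is attached to the cost-utility analysis only. No perspective is named for the comparison of cost with ED attendance. Nothing says that outside costs are excluded from the cost-utility ratio, and nothing says that they are included.

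**The case against.** The best defence is that substitution is taken seriously. Outpatient care moved within the hospital is item (c), care outside is recorded and costed, and insurer data are sought. The sentence that introduces the list promises access to all care used, so the missing inpatient item may be a slip in drafting. A provider perspective is a legitimate and openly stated choice, and the exact make-up of the numerator is something an article may leave to a fuller document.

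Much of this stands, and it rules out several stronger readings:

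- A reader might infer that all care moved out of the ED is booked as a saving. Item (c), the notebook costing and the insurer data contradict that.
- A reader might infer that the provider perspective removes general practice, community and other-hospital care from every economic result. The article does not define the perspective that way and applies it only to the cost-utility analysis, so the efficiency hypothesis is not shown to be unanswerable.
- A reader might infer that the error can only favour the intervention. Better linkage to primary care could also reduce planned stays.
- A sum in francs would need an assumed rate of re-routed stays and an assumed unit cost. Neither is in the article.

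The defence does not remove the inpatient gap. The four items are stated as the composition of in-hospital cost, and the ED/non-ED distinction is drawn explicitly for outpatient care. That is a stated scope, and condensation does not explain it. If it is a slip, it still has to be corrected.

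**Conclusion.** The point holds in two parts.

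First, the in-hospital list omits inpatient stays not induced by an ED attendance, although the data are at hand. This is plain from the text. The resulting bias in the between-arm cost difference equals the difference between the arms in the cost of those stays. That it would favour the intervention is plausible, on the assumption that case management turns some ED-led admissions into referred ones, but it is not certain. The size cannot be computed from the article.

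Second, the provider perspective and the outside-hospital costs are left unreconciled. This calls for clarification; it is not proof that those costs are excluded.

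The matter concerns a secondary outcome and leaves the primary analysis of ED visits untouched. It still deserves correction, because reducing costs is part of the stated primary aim.

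**What to change.** 1. Add item (e) to the in-hospital list: inpatient resources used within the hospital that are not related to an ED attendance, drawn from the databases already to be accessed. The definition of cost then no longer depends on the route of admission.
2. State which cost streams (items (a) to (e), notebook costs, insurer or provider data) enter the cost-utility ratio and which enter the comparison of cost with ED attendance, and name the perspective for each.
3. Report a result that includes the outside costs alongside the provider-perspective result. Which of the two is the main analysis is a judgement for the trial team: the wider one suits the question of substitution better, but rests on data that are self-reported, simulated or dependent on consent.

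The cost is mostly wording plus one further extraction from the hospital databases. Collection of the outside costs is already planned.
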